## Introduction

There is currently a disparity between demand and available resources for colonoscopies and CT colonography (CTCs) within the National Health Service (NHS). Before the COVID-19 pandemic, around 300 000 patients were being referred annually to NHS trusts suspected of having colorectal cancer (CRC) and this number was rising.^1^ Most patients referred with suspected CRC are offered an invasive colonoscopy or CTC examination, but only 30% of these participants have significant bowel disease (SBD).^2^ SBD is defined as CRC, adenomatous polyps or inflammatory bowel disease (IBD).^3^ The remaining 70% have a normal examination with 30% of those having functional conditions such as irritable bowel syndrome (IBS).

Set against this there will remain a capacity shortfall for colonoscopies and CTCs for the foreseeable future. This limits capacity of the NHS to extend CRC detection within the Bowel Cancer Screening Programme (BCSP) or to investigate those who present through the emergency department. The imbalance between capacity and demand, coupled with a lack of an accurate triage test makes it difficult for the NHS to stratify patients who present with bowel symptoms to those most at risk of SBD. In the COVID-19 era, faecal immunochemical testing (FIT) is being introduced to triage patients who present with lower gastrointestinal (GI) symptoms.^4^ However, almost all patients still receive a colonoscopy or alternative colonic imaging at some time and the optimum threshold for FIT has yet to be determined. The National Institute for Health and Care Excellence (NICE) have recommended 10
μ
gHb/g faeces,^5^ whereas the BCSP have set a cut-off of 120
μ
gHb/g faeces.^6^ Even at the lower threshold some SBD cases can be missed.^2 7 8^ Previous data have shown that FIT alone (at a threshold of 7
μ
gHb/g faeces) has a sensitivity of 80%, 53% and 86% for CRC, adenomatous polyps and IBD respectively.^2^ A lower FIT threshold may reduce the number of false negatives but it will increase the number of unnecessary colonoscopies and CTCs in patients with no abnormalities (false positives). Moreover it will always miss cases of SBD where there is no bleeding, and a high proportion of malignant tumours never bleed.

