### Primary outcome analysis

The primary outcome is diagnostic accuracy (sensitivity, specificity, NPV and positive predictive value (PPV)) of the dual index test FIT and VOC analysis. The ‘or’ rule will be utilised for the primary analysis whereby a FIT result of >10 µgHb/g faeces OR a VOC result with predicted probability >0.63 implies that the participant is suspected of having SBD and needs to be referred for colonoscopy or CTC. We will report 2×2 tables of test accuracy of the dual test by the reference standard (final report from the colonoscopy examination and confirmatory histology report of SBD which is either colon cancer, colorectal adenomas or IBD), alongside summary measures of sensitivity, specificity, NPV and PPV, and their 95% CIs. These test accuracy estimates will be used in the economic model.

We will analyse the combined FIT+VOC test results as both parallel (results from both tests are interpreted in combination) and serial testing (VOC analysis only performed if FIT is negative). The ‘or’ rule will be considered in the interpretation of both parallel and serial tests where the diagnosis is positive when either test is positive, and negative when both results are negative. In the serial test, if the FIT is positive, then the diagnosis is positive. If FIT is negative we will use the result from VOC analysis and if that is positive then the diagnosis is positive. Mathematically, both methods should give the same diagnostic results but will make a difference in the economic model.

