### Secondary outcome analyses

Secondary outcomes include: ROC of FIT plus VOC to develop an optimum thresholds for SBD detection; sensitivity, specificity, PPV and NPV estimates and their corresponding 95% CI for each individual condition of SBD (CRC, colorectal adenomas and IBD) by each individual test and combination rules; compliance rates (return of samples); the types of SBD and microscopic colitis, and the number of cases missed by CTC, FIT and VOC analyses; potential number of avoidable colonoscopies and CTCs in patients without SBD; total NHS and personal social services costs and total quality of adjusted life years (QALY) associated with each option. To find the optimal thresholds of FIT and VOC we will first plot the ROC curves of both tests individually to find the individual optimal thresholds (the one that gives the greatest specificity while achieving 97% sensitivity). Second, we will plot combinations of the two tests in the ROC space and similarly, choose the combination of thresholds which has greatest specificity while achieving the required 97% sensitivity to avoid colonoscopy. The combined thresholds of FIT and VOC in the ROC space are calculated by combining every unit of FIT (from 10 to 120µgHb/g faeces) with every unit of the predicted probability of VOC (from 0.63 to 1). Both the ‘or’ and ‘and’ rules will be explored when combining the FIT and VOC results to define a case as either SBD positive or SBD negative. If both tests are in discordant then the diagnosis is negative. For each of the thresholds that we derive from the ROC curves, we will also report the NPV estimates. This will produce an overestimate of test accuracy, which we will use as a sensitivity analysis in the economic model, as a more optimistic assumption to demonstrate the range of uncertainty.

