### Economic evaluation

An economic analysis will be carried out to determine the costs, benefits and overall cost-effectiveness of FIT +VOC versus FIT alone in selecting patients for colonoscopy or CTC among those with GI symptoms referred for investigation. The analysis will be carried out primarily from the perspective of NHS and it will employ a de novo analytic model built as part of this study. In line with recent literature,^7^ it is envisaged that the model will employ a multi-part structure, consisting of a decision tree to evaluate short-term cost and consequences accruing at the diagnosis stage followed by a state-transition model to capture the long-term (lifetime) outcomes associated with the diagnosed condition.

Calculations will consider key costs and consequences, including the costs and disutility associated with having a colonoscopy. Key model input will be drawn from the RECEDE study, including parameters related to the diagnostic characteristics of the compared options, estimates of the rate of adverse outcomes associated with colonoscopies (eg, bowel perforation and bleeding) and CTCs, as well as primary and secondary care resource use and preference-based health-related quality of life (utility) values associated with colonoscopy. The latter information will be needed to reflect the fact that undergoing a colonoscopy, including the bowel preparation and the procedure itself is an unpleasant activity which is likely to result in a temporary decrease in quality of life. Estimates of changes in quality of life will be obtained by administering a widely used and recommended generic questionnaire (EuroQol-5 Dimension-5 Level^21^) to a sample of 370 participants (20% of the total study sample) scheduled to undergo colonoscopy or CTC at (1) baseline (ie, when participant consent is received) (2) immediately prior to colonoscopy once the participant has fully completed bowel preparation, (3) 24 hours after the colonoscopy examination, (4) 72 hours post colonoscopy and (5) 3 weeks post colonoscopy. Use of resources, including NHS care, out of pocket payments and loss of income the participants may occur as a result of their colonoscopy will also be collected through patient questionnaires administered to the same sample of participants at 3 weeks post colonoscopy or CTC.

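### No planned analysis sets FIT+VOC directly against FIT alone at a lower cut-off, so a gain in detection would not by itself show that VOC adds information beyond referring more people

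*Protocol article*

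**What the plan says.** All references are to the protocol article.

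- **Introduction.** It says that "the optimum threshold for FIT has yet to be determined" and that "A lower FIT threshold may reduce the number of false negatives", at the price of more false positives. It cites FIT-alone sensitivities at a cut-off of 7 µgHb/g of 80% (CRC), 53% (adenomatous polyps) and 86% (IBD). Its closing objective is whether FIT plus VOC improves detection of SBD compared with FIT alone.
- **Stool sample analysis and Primary outcome analysis.** A positive FIT is >10 µgHb/g, and no other definition is given. The primary rule reads: "The ‘or’ rule will be utilised for the primary analysis whereby a FIT result of >10 µgHb/g faeces OR a VOC result with predicted probability" above 0.63.
- **Secondary outcome analyses.** For the single tests, "we will first plot the ROC curves of both tests individually to find the individual optimal thresholds", meaning "the one that gives the greatest specificity while achieving 97% sensitivity". For the pair, the plan will "choose the combination of thresholds which has greatest specificity while achieving the required 97% sensitivity to avoid colonoscopy". The combinations come from "combining every unit of FIT (from 10 to 120µgHb/g faeces" with VOC probabilities from 0.63 to 1, under both 'or' and 'and' rules. The article calls the resulting accuracy an overestimate and uses it in the economic model as a more optimistic sensitivity analysis.
- **Economic evaluation.** Two options are compared, "overall cost-effectiveness of FIT +VOC versus FIT alone in selecting patients for colonoscopy or CTC", and the result is a cost per additional QALY of one over the other. No cut-off is stated for FIT alone.

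**The concern.** An 'or' rule adds positives to those FIT already finds. So does lowering the FIT cut-off, and that needs no second test. A comparison of FIT+VOC with FIT >10 therefore mixes two effects: the information VOC carries, and the larger share of participants referred. To separate them, FIT+VOC has to be compared with FIT alone at a cut-off that refers about as many people.

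If that comparison is not made, FIT+VOC could appear to improve detection although a lower FIT cut-off would detect as much for the same number of examinations and without the cost of VOC. A cost per QALY against FIT >10 alone could then rest on a comparator that is not the relevant next-best option. The article expects its results to inform a revised NICE pathway.

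**Working it through.** **1. The plan's own figure.** At sensitivity 0.97 and n = 200 the Zhou-Li interval runs from 0.939 to 0.988, a width of 0.049, which meets the stated 5%. Then 200/0.19 = 1052.6, giving 1053, and 1053/0.55 = 1914.5, giving 1915. The sample size reproduces. The 200 SBD cases are used below.

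**2. Direction of the primary contrast.** Let F be FIT >10 and V be VOC >0.63.
- Se(F or V) = Se(F) + P(V+, F− | SBD) ≥ Se(F).
- Sp(F or V) = Sp(F) − P(V+, F− | no SBD) ≤ Sp(F).

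Both hold for any V, including a random one.

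**3. Can FIT alone be matched at 97%?** At a cut-off of 7, SBD sensitivity is a weighted mean of 80%, 53% and 86%, so it is at most 86% for any case mix. On these figures a FIT-alone threshold reaching 97% would have to lie below 7, if one exists. The Introduction adds that FIT will always miss SBD that does not bleed.

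**4. Can the combined grid be matched at 97%?** The grid moves only upward from the primary cut-offs (FIT from 10, VOC from 0.63). Reading its cut-offs with the same inequality as the primary rule:
- under 'or', raising either cut-off can only remove positives;
- under 'and', positives are a subset of the 'or' positives.

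No grid point can therefore exceed the primary rule's observed sensitivity. If that is below 97%, no combination qualifies. With 200 cases, 97% is 194 detected, and P(X ≤ 193) for X ~ Bin(200, p) is:
- p = 0.97: 0.39
- p = 0.96: 0.69

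**5. Illustration on assumed inputs.** The article gives none of these: FIT >10 with sensitivity 60–70% and specificity 80%; an uninformative VOC positive in 30% of everyone; an equal-variance binormal curve for FIT.
- 'Or' rule, sensitivity: 0.60 + 0.40 × 0.30 = 0.72; 0.70 + 0.30 × 0.30 = 0.79.
- 'Or' rule, specificity: 0.80 × 0.70 = 0.56.
- FIT alone lowered to specificity 0.56: Φ[probit(Se) + probit(0.80) − probit(0.56)] = Φ(0.253 + 0.842 − 0.151) = 0.83 for Se 0.60, and Φ(0.524 + 0.842 − 0.151) = 0.89 for Se 0.70.

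Matching on referral rate at 19% prevalence gives much the same result:
- For Se 0.60 the 'or' rule refers 0.19 × 0.72 + 0.81 × 0.44 = 0.493. FIT alone refers that share at sensitivity 0.813 and specificity 0.582 (0.19 × 0.813 + 0.81 × 0.418 = 0.493).
- For Se 0.70 the share is 0.19 × 0.79 + 0.81 × 0.44 = 0.507, reached by FIT alone at sensitivity 0.878 and specificity 0.581.

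These FIT-alone values are an upper view, because non-bleeding disease caps what FIT can find.

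**6. Precision of the missing contrast.** For a paired sensitivity difference near zero in 200 SBD cases, with assumed discordance between the two rules of 10% to 40%, the 95% half-width is 1.96 × √(0.10/200) = 0.044 to 1.96 × √(0.40/200) = 0.088. This treats the cut-off as fixed.

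**The case against.** A reader might infer that FIT alone is examined only at >10 and that the study cannot tell whether VOC adds anything. The article does not support that. It plans a ROC curve for FIT by itself and a FIT-alone threshold chosen by the same criterion as the combinations. The 10 to 120 range is stated for the combined grid only and sets no floor on the single-test curve. The economic section states no FIT-alone cut-off, so >10 there is an inference from the other sections. If both 97% thresholds exist, comparing their specificities is a fair matched comparison, and a failure of FIT alone to reach 97% would also be informative.

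Other points on that side also have force:
- The Introduction gives 10 as the NICE-recommended cut-off, an ordinary reason to use it as the current-practice comparator, and gives a reason why FIT alone has a ceiling.
- Specificity and PPV are reported beside sensitivity, and the model charges cost and disutility for colonoscopy, so extra referrals are not hidden.
- A wholly worthless VOC would show a diagonal ROC curve of its own. The cited VOC sensitivities of 80%, 92% and 86% suggest it is not worthless.
- A condensed article may leave the list of model strategies to a fuller document.

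These points rule out the stronger reading but leave the gap. FIT alone failing at 97% does not show whether FIT at a lower cut-off does as well as FIT+VOC at the same referral rate. A good VOC curve of its own does not show what VOC adds given FIT. No contrast between the two optima is named, and the derived thresholds reach the model only as an optimistic sensitivity analysis, not as an added comparator. The article does state the form of the economic comparison, and it has two options.

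**Conclusion.** The concern holds in a limited form. The plan varies FIT alone across its ROC curve, but it names no direct comparison of FIT+VOC with FIT alone at a lower cut-off, either for accuracy or in the model. Against FIT >10, the direction of the sensitivity contrast is fixed by the 'or' rule. The one route to a matched comparison, at 97% sensitivity, may fail on either side. FIT at 7 reaches at most 86% on the cited figures. The combined grid has no qualifying point whenever the primary rule is observed below 97% (39% probability if its true sensitivity is 97%, 69% if 96%).

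The first statement is algebra. The probabilities rest on 200 cases and binomial sampling, and the 86% on earlier data that may not carry over. The contrast of 72–79% with 83–89% only illustrates how a worthless second test could show a gain; it does not predict what this study will find.

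This should be changed because it bears directly on the stated objective and the change is cheap.

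**What to change.** The additions below are comparators for evaluation and propose no clinical cut-off.

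- **Secondary outcome analyses:** report the paired difference in sensitivity, with its 95% CI, between FIT+VOC and the FIT-alone cut-off that refers the same proportion of participants. Allow for that cut-off being chosen in the same data, for example by bootstrapping the whole procedure.
- **Economic evaluation:** state the FIT-alone cut-off used in the base case. Add FIT alone at lower reportable cut-offs (for example 7, which the Introduction cites) as strategies. Present a full incremental analysis over all strategies instead of one pairwise ratio.

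The planned FIT ROC curve already needs numeric FIT values, so there is no new sampling and no change to any participant's care. The cost is extra model runs. The benefit shown for VOC may turn out smaller, and on the assumed discordance the paired contrast would be known to within about 4 to 9 percentage points.

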### Peer review and patient and public involvement

The RECEDE study has been peer reviewed in the NIHR HSDR process by external reviewers and the commissioning board. This protocol has also been reviewed externally by a Trial Steering Committee and internally by the Trial Management Group. The study was also reviewed by members of the GUT club (survivors of GI cancer) and the patient and public involvement in research (PPI) at the sponsor site. Both groups were supportive of the aims of RECEDE and agreed further evidence is required for the utility of FIT and VOC analysis in diagnosing SBD.

## Ethics and dissemination

Ethical approval was provided by Liverpool Central Research Ethics Committee (20/NW/0346). The study will be conducted in compliance with the principles of the International Conference on Harmonisation (ICH) GCP guidelines and in accordance with all applicable regulatory guidance. The study will comply with the current Data Protection regulations and regular checks and monitoring will be undertaken by the study manger to ensure compliance.

Results from RECEDE will naturally be of profound interest to clinicians worldwide who investigate lower GI symptoms. Results can also be used by NICE to inform a revised pathway for managing participants with lower GI symptoms—to categorise high risk, that is, those with SBD versus low risk (without SBD). Those with very low risk of SBD could potentially be managed in primary care without need to refer to secondary care. RECEDE will lead to high level presentations at GI and Oncological meetings both nationally and internationally. It will also result in high quality open access manuscripts. A range of dissemination products will include annual reports, national publications, press releases through UHCW Communications Department, participant safety collaborations, presentation and talks as well as videos will ensure that all audiences can be updated. Dissemination of results to participants will be led by our PPI coapplicant and facilitated through GUTs UK which is the partner charity of the British Society of Gastroenterology. We will also engage with key stakeholders including PPI groups, local specialised colorectal Clinical Research Group, as well as Cancer Alliance groups
